#### Criteria for Discontinuing or Modifying Allocated Interventions

Participants are free to withdraw from the study at any time and for any reason. As it has been previously mentioned, according to the patient-centered approach that we follow, we have been prepared to adapt our dance intervention following possible differentiation in circumstances (domain 6, Textbox 1). DfPD classes are generally characterized by supportive instruction in a way that participants feel free to perform each dance combination at their individual level of functionality [67]; thus, any personal modification or interpretation is always encouraged to be performed by each participant (domain 7, Textbox 1).

### Outcomes

#### Primary Outcomes

Patients’ QoL before and after each research period will be assessed by the change in total score of the Greek version [94] of Parkinson’s Disease Questionnaire-8 [95], which is a 0-to-100-point scale with a higher score indicating worse QoL.

#### Key Secondary Outcomes

The expected key secondary outcomes are outlined in Textbox 3.

Key secondary outcomes.
**Safety (occurrence of adverse events and serious adverse events)**
The occurrence of adverse events such as possible falls, injuries, muscle soreness, and excessive fatigue [96] will be assessed by recording after the end of the program, as has been done in our past pilot clinical study [45], for each participant. The following are considered as serious adverse events [96,97], and they will be recorded after the end of the program: death, threat to life, hospitalization, persistent or significant disability or incapacity, and necessity of surgical operation for any of the aforementioned events.

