**Methods:**

This is a 3-arm crossover randomized controlled trial (in-person DfPD vs online DfPD vs control) of UPGRADE-PD (Upbeating Greek Application of Dance in Parkinson’s Disease). The experimental period will be 10 months, including three 2-month interventional periods of two 60-minute dance classes per week for each group (in-person DfPD vs online DfPD) versus a control group (nonintervention group), and two 2-month washout periods between each group for 40 Greek patients with early- to midstage PD. Assessments will be performed face-to-face at baseline and at the end of each study period and will include quality of life, fatigue, depressive symptoms, stress, anxiety, sarcopenia, frailty, balance, cognitive functions, movement and nonmovement PD symptoms, and BMI. Safety, feasibility, and patient satisfaction for each dance intervention (in-person DfPD vs online DfPD) will be assessed as well.

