## Methods

### Study Design

This is a single-centered 3-arm crossover and open-label randomized controlled trial (in-person DfPD vs online DfPD vs control) of UPGRADE-PD (Upbeating Greek Application of Dance in Parkinson’s Disease). Blinding among participants and researchers is not possible due to the nature of the study. There are 6 possible research sequences, as shown in Table 1, and 3 possible carryover effects (1, 2, and 3) for each period from the prior intervention, as shown in Table 2. The study will last 10 months for each participant, including three 2-month research periods and two 2-month washout periods. Assessments will be conducted at enrollment (T_−0_=week −1), baseline periods (T_0_=week 0, T_2_=week 18, and T_4_=week 36), and postinterventional periods (T_1_=week 9, T_3_=week 27, and T_5_=week 45), as shown in Table 3. Allocation to each of the 6 possible sequences will occur after the completion of the first baseline assessment, as shown in the participant flow in Figure 1.

**Table 1 table1:** The UPGRADE-PD (Upbeating Greek Application of Dance in Parkinson’s Disease) study design.

Sequence	Period		
	First	Second	Third
ABC	A^a^	B^b^	C^c^
BCA	B	C	A
CAB	C	A	B
ACB	A	C	B
BAC	B	A	C
CBA	C	B	A

^a^Intervention A (in-person Dance for Parkinson’s Disease combined with usual medical care).

^b^Intervention B (online Dance for Parkinson’s Disease combined with usual medical care).

^c^Control group (usual medical care without Dance for Parkinson’s Disease).

**Table 2 table2:** The UPGRADE-PD (Upbeating Greek Application of Dance in Parkinson’s Disease) study’s code for the possible carryover effect.

Sequence	First period		Second period		Third period	
	Trial	Carryover effect	Trial	Carryover effect	Trial	Carryover effect
ABC	A^a^	0^b^	B^c^	1^d^	C^e^	2^f^
BCA	B	0	C	2	A	3^g^
CAB	C	0	A	3	B	1
ACB	A	0	C	1	B	3
BAC	B	0	A	2	C	1
CBA	C	0	B	3	A	2

^a^Intervention A (in-person Dance for Parkinson’s Disease combined with usual medical care).

^b^Noneffect.

^c^Intervention B (online Dance for Parkinson’s Disease combined with usual medical care).

^d^Effect from intervention A.

^e^Control group (usual medical care without Dance for Parkinson’s Disease).

^f^Effect from intervention B.

^g^Effect from the control group.

**Table 3 table3:** The UPGRADE-PD (Upbeating Greek Application of Dance in Parkinson’s Disease) schedule of enrollment, interventions, and assessments for participants.

Time point (wk)		Study period									

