		Enrollment (T_–0_=wk –1)	Baseline 1 (T_0_ =wk 0)	Allocation (T_0_ =wk 0)	Postintervention 1 (T_1_ =wk 9)	Wash-out 1 (T_1_ =wk 9)	Baseline 2 (T_2_ =wk 18)	Postintervention 2 (T_3_ =wk 27)	Wash-out 2 (T_3_ =wk 27)	Baseline 3 (T_4_ =wk 36)	Postintervention 3 (T_5_ =wk 45)

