Procedures that will be performed during the study.The assessment is structured, for research reasons; it is characterized by empathy, and includes multiple movement and nonmovement aspects of Parkinson disease (PD), giving a full informative description of the study’s procedures and goals to participants by the main researcher (ME), who is a specialized neurological diseases physiotherapist, and an adapted physical and dance educator. Although ME is responsible for the whole communication with patients, assessments before and after each research period will be performed by an independent researcher who is specialist in the use of the specific tools to eliminate possible detection bias. Part of the assessment (Movement Disorder Society–sponsored revision of the Unified Parkinson’s Disease Rating Scale [MDS-UPDRS] and Montreal Cognitive Assessment [MoCA] tests) will be performed by specialized neurologists of the Eginition Neurological Outpatient Clinic (domains 1 and 3).Each step of the assessment procedure before and after each research period is explained; the necessity that each patient gives continuous feedback about possible adverse events is emphasized (domain 2).Translated and validated scientific tools are used, and a continuous multidisciplinary scientific collaboration between physicians, nurses, and physiotherapists is ensured as part of this study (domain 3).Therapeutic intervention goals were based on past research; however, personal patient needs were adapted in the dance combination’s design, based on our past pilot study [45], while individual music preferences were considered for the dance intervention’s design [66] (domain 4).A high-confidence environment, accompanied by emotional support, empathy, and respect between participants and the physiotherapist, will be ensured (domain 5).Although the early- to midstage severity stage of PD of participants usually does not demand specific modifications for each participant, due to the related motor independence with low fall risk [40], we are prepared to adapt our dance intervention following possible individual circumstances (domain 6).Dance for Parkinson’s Disease (DfPD) classes are generally characterized by supportive instruction in a way that participants feel free to perform each dance combination in their individual level of functionality [67]; thus, inclusion, adaptability, and accessibility to all are promoted during each dance class [68] (domain 7).The dance intervention is being conducted in a facility that is offered for free. Classes will be conducted solely by the main researcher (ME), while the trial will be partially funded by a charitable association, and continuous accessibility of patients to the research team will be provided (domain 8).

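### The only time fixed for recording adverse events is after the end of the program (week 45), a weak basis for judging safety by dance intervention in a three-period crossover

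*Protocol article*

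**What the plan says.** In the protocol article, Textbox 3 (Safety) names falls, injuries, muscle soreness and excessive fatigue as examples of adverse events. It says that their occurrence "will be assessed by recording after the end of the program", following the earlier pilot study, for each participant. For serious adverse events the rule is "they will be recorded after the end of the program: death, threat to life, hospitalization", followed by disability and surgery.

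Table 3 agrees. The row for adverse and serious adverse events has one tick, in the last column, headed "Postintervention 3 (T_5_ =wk 45". The PDQ-8 and the other clinical scales are ticked at all six visits. Study Design places those visits at "baseline periods (T_0_=week 0, T_2_=week 18, and T_4_=week 36" and "postinterventional periods (T_1_=week 9, T_3_=week 27, and T_5_=week 45".

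The Abstract (Methods) promises more than an overall statement on safety. Its sentence opens with safety and feasibility and ends "patient satisfaction for each dance intervention (in-person DfPD vs online DfPD) will be assessed as well". The Objective section makes the safety of both interventions part of the key secondary aim.

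Textbox 2 (domain 2) points another way: "the necessity that each patient gives continuous feedback about possible adverse events is emphasized". It names no form, time or person for recording that feedback. Data Collection and Management provides for noting reasons for withdrawal where possible and mentions no adverse event enquiry at that point.

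**The concern.** The recording rule comes from a pilot that, according to Sample Size, was uncontrolled and tested in-person dance only. There, every event belonged to the one intervention. Here each participant passes through in-person dance, online dance, control and two washouts, and a single recording after all of them must be split between conditions.

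Soreness, excessive fatigue and minor falls are easy to forget and hard to date months later. Late recording therefore threatens both the count and the assignment to a condition. Under-counting leans towards a conclusion of safety. Misplacing events between periods dilutes a real difference between in-person and online delivery. The online result matters particularly, because the section on the choice of comparators says that no data exist from a related online study. A participant who leaves early may also not be there to be asked.

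**Working it through.** The protocol gives no figure to reproduce here. The check has two parts: what the recording phrase means, and what delay follows if the rule is applied as written.

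**Meaning of the phrase.**
- For measurement by period, Primary Outcomes and most of Textbox 4 refer to assessment before and after each research period. Textbox 3 uses different words for safety.
- The patient satisfaction part of Textbox 3 places one interview about both in-person and online dance after the end of the program. Both interventions must be finished by then.
- So the phrase most naturally means the end of the study, not the end of each period. The single week-45 tick fits that reading.

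**Delay from event to recording.** Inputs are the visit weeks in Study Design. Delay = 45 minus week of event.

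| Interval | Weeks | Shortest delay | Longest delay |
|---|---|---|---|
| Period 1 | 0–9 | 45 − 9 = 36 | 45 − 0 = 45 |
| Washout 1 | 9–18 | 45 − 18 = 27 | 45 − 9 = 36 |
| Period 2 | 18–27 | 45 − 27 = 18 | 45 − 18 = 27 |
| Washout 2 | 27–36 | 45 − 36 = 9 | 45 − 27 = 18 |
| Period 3 | 36–45 | 45 − 45 = 0 | 45 − 36 = 9 |

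**Share of exposures affected.** In Table 1 each condition stands in each period in 2 of the 6 sequences. Periods 1 and 2 together hold 4/6, about two thirds, of the exposures to each condition. Events in these would be recorded at least 18 weeks late.

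**Does the delay favour one condition?** The mean delay from period end to week 45 is (2 × 36 + 2 × 18 + 2 × 0)/6 = 108/6 = 18 weeks for in-person, online and control alike. With 40 participants in 6 sequences (40/6 = 6.67 each) the balance is near rather than exact. By design, the delay does not systematically favour one condition.

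**Withdrawals.** Sample Size expects dropout of up to 15%, and Results reports 40 randomized. The upper figure is 0.15 × 40 = 6 participants not present at week 45. At assumed rates of 5% and 10% it would be 2 and 4.

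**The case against.** The strongest reply is that week 45 marks when results are compiled. Adherence, attrition and recruitment rates carry the same single tick in Table 3, and their data must arise earlier. This stands: the tick alone is weak evidence. What carries the point is the wording of Textbox 3, which places the recording itself after the end of the program, for both adverse and serious events.

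A reader might infer that events are certainly collected once, by recall at a final visit. The document does not go that far. Textbox 2 asks for ongoing feedback and promises continuous access to the research team, and one investigator teaches every class. The list of serious events includes death, which no participant can report, so recording cannot depend wholly on attending T5. Ongoing feedback and recording at the end can coexist. The places need reconciling; they do not flatly contradict each other.

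A reader might also infer that events in dropouts are lost. That too is unsupported. Textbox 3 says that recording is for each participant, an event that causes withdrawal may be captured as its reason, and 15% is an upper limit. Nothing in the document shows that those who leave are the ones most likely to have had an event.

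Finally, an article may leave event forms and reporting procedures to the full protocol, so their absence is no fault. The point here is a recording time that the article does state, and states badly.

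**Conclusion.** The concern holds in a limited form. The only recording time the protocol fixes for adverse and serious adverse events is after the end of the program, shown as week 45. That suits a safety assessment by intervention poorly, and it is not reconciled with the feedback asked for in Textbox 2.

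The delays of 36 to 45 weeks for period 1 and 18 to 27 weeks for period 2 apply if events are first recorded at week 45. On that assumption events may be under-counted and put in the wrong period. A reader might conclude that the in-person versus online comparison is biased towards one arm, but the near-balanced sequences do not support that; the effect is blurring. For withdrawals, the supportable statement is that events in up to 6 of 40 participants are at risk of being missed. The primary PDQ-8 analysis is unaffected.

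**What to change.** Add ticks for adverse and serious adverse events in Table 3 at T1, T2, T3 and T4, keeping T5, so that each period and each washout closes with a recording. Note for every event its date and the condition the participant was in. Record serious events when they become known, and ask about adverse events at withdrawal. Amend Textbox 3 to match, and say in Textbox 2 how ongoing feedback is written down. Report events per participant exposed, by condition. The protocol promises safety results only for the two dance interventions; the control periods would serve as a reference.

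If continuous logging already takes place, one sentence is enough: events are logged as they occur, and week 45 is when they are tabulated.

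The visits already exist, so the cost is a little extra recording work. The article describes recruitment as concluded and the trial as ongoing, so new ticks cannot recover periods already completed. Where no log was kept for those, state the limitation beside any safety conclusion.

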**Feasibility**
Adherence rates: an adherence rate of ≥70% is considered as high in older patients with functional limitations [98], and it will be used to assess adherence to each dance intervention following the appropriate formula after the end of the program:

Attrition rates: an attrition rate of ≤15% is considered as acceptable by the Physiotherapy Evidence Database Scale [99], and will be used to assess attrition to each dance intervention following the appropriate formula after the end of the program:

Recruitment rates: for the assessment of the recruitment rates, a target of up to 5 months for 40 participants will be accepted according to past studies [45,100] after the end of the program.
**Patient satisfaction**
Willingness to continue the program after the intervention: a verbal statement for continuing the program after the end of the intervention in a 6-point Likert scale (0=I don’t know if I’d like to continue the program, 1=I don’t want to continue the program at all, 2=I don’t want to continue the program, 3=I might want to continue the program, 4=I want to continue the program, and 5=I want to continue the program very much) after the end of the program.Advantages and disadvantages of the program: there will be a total of 2 open questions: (1) Could you please list all the positive and negative points of the in-person Dance for Parkinson’s Disease (DfPD) intervention? and (2) Could you please list all the positive and negative points of the online DfPD intervention? These will be asked in a one-to-one interview of each participant by the principal investigator (ME) after the end of the program for the qualitative recording of advantages and disadvantages of each dance intervention from the patient’s perspective.

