**Assessments**											
	SD^d^ and MH^e^		✓								
	AE^f^ and SAE^g^										✓
	Adherence rates										✓
	Attrition rates										✓
	Recruitment rates										✓
	Patient satisfaction										✓
	PDQ-8^h^		✓		✓		✓	✓		✓	✓
	PFS-16^i^		✓		✓		✓	✓		✓	✓
	MFIS^j^		✓		✓		✓	✓		✓	✓
	DASS-21^k^		✓		✓		✓	✓		✓	✓
	SARC-F^l^		✓		✓		✓	✓		✓	✓
	EWGSOP2^m^		✓		✓		✓	✓		✓	✓
	FP^n^		✓		✓		✓	✓		✓	✓
	BBS^o^		✓		✓		✓	✓		✓	✓
	MoCA^p^		✓		✓		✓	✓		✓	✓
	MDS-UPDRS^q^		✓		✓		✓	✓		✓	✓
	BMI		✓		✓		✓	✓		✓	✓
	Music preferences	✓									

^a^DfPD: Dance for Parkinson’s Disease.

^b^A: starting point of the period.

^c^B: ending point of the period.

^d^SD: sociodemographics.

^e^MH: medical history.

^f^AE: adverse event.

^g^SAE: serious adverse event.

^h^PDQ-8: Parkinson’s Disease Questionnaire-8.

^i^PFS-16: Parkinson Fatigue Scale-16.

^j^MFIS: Modified Fatigue Impact Scale.

^k^DASS-21: Depression, Anxiety, and Stress Scale-21.

^l^SARC-F: Strength, Assistance in walking, Rise from a chair, Climb stairs, and Falls Scale.

^m^EWGSOP2: European Working Group on Sarcopenia in Older People.

^n^FP: Frailty Phenotype.

^o^BBS: Berg Balance Scale.

^p^MoCA: Montreal Cognitive Assessment.

^q^MDS-UPDRS: Movement Disorder Society–sponsored revision of the Unified Parkinson’s Disease Rating Scale.

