### Sample Size

A prospective, nonrandomized, uncontrolled, open-label pilot study has already been conducted in a Greek population of 16 patients with early- to midstage PD, showing that in-person DfPD is safe and feasible, and can improve QoL, as well as several movement and nonmovement PD symptoms [45]. According to the results of the above pilot clinical trial for our primary outcome (QoL), the Cohen equations for sample size calculation [124], and considering the power of the study equal to 80% and the level of statistical significance of the controls equal to the conventional limit of statistical significance (α=.05), a power analysis was applied with the a priori formula for the *F* test statistical control through analysis of variance with repeated measures using G*Power software (version 3.1) [125].

Taking in consideration that the number of experimental groups will be 3, the number of repeated measurements for each participant will be 6, and the average correlation coefficient between repeated measurements will be 0.64, it was estimated that for this study, which has a 1:1:1:1:1:1 distribution ratio of participants to the groups, at least 6 participants are required in each group (18 in total). On the basis of the equations that adjust the sample size to the expected dropout rate [126], which is expected to be up to the 15% acceptable value, based on the Physiotherapy Evidence Database Scale [99], the minimum sample size required to achieve the study’s primary end point (QoL) is 21 participants.

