### Data Collection and Management

All assessments will be conducted face-to-face by an independent investigator to eliminate possible detection bias, except of the Movement Disorder Society-Unified Parkinson’s Disease Rating Scale and Montreal Cognitive Assessment, which will be conducted face-to-face by specialized neurologists of the Eginition University Hospital Neurological Outpatient Clinic.

Participants are free to quit at any time if they wish to discontinue the study. In that case, reasons for withdrawal will be recorded, if this is possible. Participant’s enrollment will be followed by the research team’s assistance during the entire study period, including scheduling of data collection appointments, reminding of intervention’s appointments, and communicating the starting time of each research period.

Data, including consent forms, completed paper-based data files, and study notes, will be securely stored in the main investigator’s office, which will be locked. Raw data will be encrypted and stored digitally on a local computer with access rights to the main investigator. All original data will be archived for 5 years after the completion of the research and then destroyed, according to local regulations. All written data will be stored in a locked cabinet of the main investigator’s locked office for 5 years and then destroyed. Digital data will be stored on a password-protected local computer.

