### Statistical Analysis

The primary analysis will evaluate the between group differences in total score of the Greek version of Parkinson’s Disease Questionnaire-8 after each research period. Mean (SD) or summary statistics appropriate to the distribution of the QoL total score will be reported by study group (in-person DfPD vs online DfPD vs control). Study groups will be compared in terms of QoL using mixed model repeated measures considering the correlated data from the same patient [128]. Mixed model repeated measures are robust in small sample size studies; thus, a decreased risk of type II errors occurs [129]. For all secondary end points, summary statistics will be tabulated by study group, and study groups will be compared with a statistical method appropriate to the type of the end point (eg, continuous and categorical end point). Bonferroni correction will be used to account for multiple comparisons of secondary outcomes.

A secondary analysis of the primary end point will adjust for those prerandomization variables which might reasonably be expected to be predictive of favorable QoL total score. Any deviations from the protocol will be recorded and agreed by the investigators. Missing data will not be imputed neither for primary nor secondary analyses, and no interim analyses will be conducted in this study. All the *P* values are 2-sided at an α level of .05. Analyses will be conducted with SPSS (version 20.0; IBM Corp) and R (version 4.4.1; R Foundation for Statistical Computing).

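### Willingness to continue is rated only at week 45, so it is likely to be missing for early leavers, and the summary among those rated may be too favourable

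*Protocol article*

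**What the plan says.** All of this comes from the protocol article.

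- **Outcome.** Key Secondary Outcomes (Textbox 3, Patient satisfaction) defines willingness to continue as "a verbal statement for continuing the program after the end of the intervention in a 6-point Likert scale", coded 0 to 5 and taken once the program has ended. Two open questions on good and bad points of each dance format are put to every participant at the same stage.
- **Timing.** In Table 3 the row "Patient satisfaction" has one tick, under the last visit (T5, week 45). The PDQ-8 and the other clinical scales are ticked at six visits.
- **Withdrawal.** Data Collection and Management states: "Participants are free to quit at any time if they wish to discontinue the study". The only thing it then seeks is the reason, where that can be obtained.
- **Expected loss.** Sample Size describes dropout as a quantity "which is expected to be up to the 15% acceptable value". Textbox 3 uses the same 15% as the feasibility limit for attrition, applied to each dance intervention.
- **Missing data.** Statistical Analysis states: "Missing data will not be imputed neither for primary nor secondary analyses".

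**The concern.** Each of these statements is unremarkable alone. Together they mean that a participant who leaves before week 45 has no scheduled occasion to give the rating, and nothing is substituted for it.

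This item is more exposed to that than most. It asks whether the person wants to go on with the program, and leaving early is plausibly related to the answer. The missing ratings are therefore unlikely to be a random subset. If leavers are on average less willing, the summary among those rated is too favourable, and more so the more people leave. The trial sets out to judge the feasibility of, and satisfaction with, two dance formats, so a reader could see high willingness reported next to attrition close to its limit, with nothing connecting the two results.

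**Working it through.** **The plan's own use of 15%.** The dropout figure enters one calculation, the step from 18 to 21 participants in Sample Size. Multiplying gives 18 × 1.15 = 20.7, rounded up to 21, as stated. Dividing gives 18 / 0.85 = 21.18, rounded up to 22. The difference of one does not matter here, because 40 were randomised. It does confirm that 15% is used as a whole-study planning loss.

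**Inputs**
- Randomised: N = 40 (Results).
- Attrition: up to 15% (Sample Size). Values of 5% and 10% are added to show the range.
- Number willing among those rated: not in the article, so assumed. The article sets no cut-off on the scale. For illustration only, willing means one of the top two categories.

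**Formulas.** Let w be the number unrated, c = N − w the number rated, x the number willing among those rated, and p = x/c.
- Rated-only proportion: x/c.
- Lower bound over everybody (no unrated person willing): x/N.
- Upper bound over everybody (all unrated persons willing): (x + w)/N.
- Largest overstatement: x/c − x/N = p × w/N.
- Largest understatement: (x + w)/N − x/c = (1 − p) × w/N.

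**At 15%:** w = 0.15 × 40 = 6 and c = 34.

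| Willing / rated (assumed) | Rated only | Bounds over all 40 | Largest overstatement | Largest understatement |
|---|---|---|---|---|
| 24/34 | 70.6% | 60.0% to 75.0% | 10.6 points | 4.4 points |
| 27/34 | 79.4% | 67.5% to 82.5% | 11.9 points | 3.1 points |
| 31/34 | 91.2% | 77.5% to 92.5% | 13.7 points | 1.3 points |
| 34/34 | 100% | 85.0% to 100% | 15.0 points | 0 points |

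**At lower attrition** the interval between the bounds has width w/N: 2/40 = 5 points at 5%, and 4/40 = 10 points at 10%.

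**Who belongs in the denominator.** Sequences CAB and CBA begin with the control period (Table 1), so someone who leaves during it has never danced and has no program to continue. If k of the 6 leavers had not danced, the largest gap over those who started dance is (6 − k)/(40 − k):
- k = 0: 6/40 = 15.0 points
- k = 2: 4/38 = 10.5 points
- k = 6: 0/34 = 0 points

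The 15-point maximum therefore needs every leaver to have started dance, every rated participant to be willing, and no leaver to be willing. The gap is 0 if nobody is unrated, or if leavers are as willing as those rated.

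**The case against.** The case against has several good parts.

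- A reader might infer that people who withdraw can never be scored, or that the result will be reported in completers only. The article says neither. It defines no completer set, does not bar contact with someone who has left, addresses its open questions to every participant, and promises patients continuing access to the research team. That stands. It does not settle the matter, because the wording about every participant belongs to the open questions rather than the rating, and gives no occasion for asking someone who has left.
- A reader might also infer that the no-imputation rule removes leavers from the denominator. It only says that missing values are not filled in. Listing all participants with a row for missing ratings would be consistent with it. That stands.
- Denominators and exit procedures are commonly left to a full protocol or analysis plan, so their absence is not itself a finding. The point rests on what the article does fix: one rating time, the one item sought at withdrawal, and no imputation.
- It is tempting to count every withdrawal as unwilling and call the lower bound the true result. The documents do not support that. Participation lasts 10 months, with a control period and two washouts, so leaving the study is not the same as rejecting the classes. Attrition is already a separate outcome.
- The item is descriptive and, unlike adherence, attrition and recruitment, has no success threshold. That limits the consequence.

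**Conclusion.** The concern holds in a limited form. As scheduled, willingness to continue is likely to be missing for participants who leave before week 45, and the summary among those rated may be biased upward. At the planned ceiling, about 6 of 40 would be affected and the overstatement lies between 0 and about 15 points. The willing counts in the working are assumptions, as is the cut-off.

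The 15% is itself a planning ceiling, not an observed loss: actual attrition may be lower. It could also be higher overall, since the feasibility limit is applied to each dance intervention separately. The upward direction rests on the plausible but untested premise that leavers are less willing than those who stay.

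The effect is confined to one descriptive key secondary outcome. This is an inexpensive improvement, not a flaw that threatens the trial's main conclusion.

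**What to change.** 1. Put the same 6-point item to any participant who withdraws after starting dance classes, when the reason for withdrawal is sought.
2. Report the numbers rated and not rated out of all who started dance.
3. Present the distribution among those rated as the main result. Beside it, give a sensitivity bound that counts unrated withdrawers as not willing, and state before analysis which categories count as willing for that bound.

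**Cost.** One extra question at withdrawal and a short reporting rule. The article describes recruitment as closed and the trial as ongoing, so the question may miss those who have already left. It also describes no formal exit visit, so some will not be reached. The reporting rule can still be fixed, because analysis is to start only after the last participant has finished. The bound will look somewhat less favourable than the rated-only figure and will count some withdrawals that had nothing to do with the program, which is why it should not be the main result.
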